### Data collection, timeline, and outcomes

#### Outcomes

The study visit schedule is detailed in Table 1. A description of the tools used to measure specific outcomes is provided below. The primary outcome measures for the pilot study are (1) feasibility, (2) acceptability, and (3) adherence with the trial protocol.

**Table 1 Tab1:** Study schedule for the participants in the pilot randomized controlled trial of fecal microbiota transplantation (FMT) treatment of bipolar depression

Measure	Study period					Purpose
	Prior to intervention		Intervention	Follow-up (12 visits every 2 weeks)		
	Screening	Baseline	Colonoscopy visit	Every 2 weeks	Week 12 and week 24 visits	
Eligibility screening	**X**					**Feasibility**
Informed consent	**X**					**Feasibility**
Confirmation of eligibility		**X**				**Feasibility**
Randomization		**X**				**Feasibility**
Colonoscopy			**X**			**Intervention**
Anthropometric measurements		**X**		**X**		**Covariates**
Food diary		**X**			**X**	**Covariates**
Mucosa biopsies/colon secretion			**X**			**Microbial analysis**
Stool sample		**X**			**X**	**Microbial analysis**
Blood sample			**X**			**Safety**
Concomitant medications	**X**	**X**	**X**	**X**		**Safety**
Symptoms diary				**X**		**Safety/tolerance**
Toronto Side Effect Scale (TSES)		**X**		**X**		**Safety/efficacy**
Mini-International Neuropsychiatric Interview (MINI)	**X**					**Feasibility**
Young Mania Rating Scale (YMRS)	**X**	**X**		**X**		**Efficacy**
Montgomery–Asberg Depression Rating Scale (MADRS)	**X**	**X**		**X**		**Efficacy**
State and Trait Anxiety Inventory (STAI)		**X**		**X**		**Efficacy**
Sheehan Disability Scale (SDS)		**X**		**X**		**Efficacy**
World Health Organization Quality of Life (WHOQOL-BREF)		**X**		**X**		**Efficacy**

##### Feasibility, clinical, tolerability, and safety outcomes

We will record feasibility data related to (i) eligibility (for example, proportion of mental health clinic patients eligible), (ii) recruitment (for example, number, nonparticipation reasons, especially the decision related to the colonoscopy aspect of the study), and (iii) timing (for example, time before participant begins treatment).

Safety of FMT will be assessed from unsolicited and solicited adverse events. Clinical and tolerability scores at baseline (Visit 2) will be compared with those at study completion (Visit 15). In addition, the Toronto Side Effects Scale (TSES) [28], a 32-item instrument designed to establish incidence, frequency, and severity of CNS, gastrointestinal, and sexual side effects will be used.

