**Methods and design:**

We describe a pilot randomized controlled trial of FMT in participants with BD depression to assess the feasibility, efficacy, safety, and tolerability of this intervention. Individuals between 18 and 65 years of age will be enrolled in the study if they meet diagnostic criteria for a major depressive episode of at least moderate severity in the context of a BD diagnosis and have not responded to treatment for BD. Participants will be randomized 1:1 to receive either screened and processed donor stool (allogenic FMT) or their own stool (autologous FMT) via colonoscopy and monitored for 24 weeks post intervention. Depressive and manic symptoms, treatment acceptability, and gastrointestinal and other side effects are assessed at baseline (prior to randomization) and weekly. Stool samples to assess microbiome composition are obtained at baseline and 3 and 6 months.

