### Intervention

Each participant receives one dose of either autologous or allogenic FMT product. FMT manufacturing will be performed as in a previous RCT (NCT01226992). Briefly, 50 g of screened donor or participant feces will be homogenized for 30 min using a Stomacher® Paddle Blender with 30 mL sterile 0.9 % NaCl + 10% glycerol in a sterile, 330-μn microfilter-separated, double-compartment polyethylene bag. The autologous FMT control arm is essential because bowel preparation and colonoscopy can induce changes to the intestinal microbiome [22, 23]. The volume of fecal filtrate corresponding to 50 g of original feces will be aliquoted, labeled with a recipient ID number to maintain blinding, and stored at – 80 °C. Freezing stool with glycerol as a cryoprotectant has been shown to yield active FMT preparations [24, 25]. For instance, frozen fecal filtrate for treatment of *Clostridium difficile* infection can be stored for at least 6 months in 10% glycerol without loss of clinical efficacy or viability of the six bacterial groups measured [26]. Similarly, clinical efficacy in treating *C. difficile* infection was shown not to differ between frozen and lyophilized FMT product after 9, 11, or 15 months [27]. An aliquot of the final fecal filtrate will be stored at – 80 °C for analysis in case retroactive testing of the fecal filtrate is required.

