##### Mucosal biopsy analysis

Of the two biopsies from each of the three locations, one will be stored in 10% formalin for pathological assessment and the other stored at – 80 °C for microbiome analysis. DNA will be extracted from 3 mg of tissue and purified as for the stool. Sequencing and analysis will be performed as for stool samples.

A baseline visit with the research coordinator (blind to group allocation) occurs in person, prior to the start of the active study phase, to collect baseline demographic and health service use information as well as baseline measures on mental health symptom scales. During all subsequent visits (visit 1 to visit 15), concomitant medications will be recorded. Anthropometric measurements (waist-to-hip ratio, and body mass index (BMI)) will be taken at every visit, except during the first visit for screening (visit 2—visit 15). Food intake will be recorded for 3 days (2 weekdays and 1 weekend day), and the completed forms will be collected during visit 2 (baseline), 9 (12 weeks), and 15 (24 weeks). To minimize confounding effects, participants will be asked to maintain their usual diet and exercise level. Participants will also itemize their food intake using a validated form developed by the Fred Hutchinson Cancer Research Center [41]. Food records will be readministered at 3- and 6-month time points. Dietary data will be analyzed using NUTRITIONIST PRO™ DIET ANALYSIS SOFTWARE (Axxya Systems) to assess intake of macro- and micronutrients.

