##### Intervention visit

At *Visit 3*, FMT will be performed. To document side effects, patients will be provided with a symptom diary after FMT, which they will submit at every subsequent study visit.

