##### Post-intervention visits

To evaluate whether FMT effects longer-term changes in depression severity and microbiome profile, patients will be followed for 6 months (24 weeks) post-FMT, during *Visits 3–15*. Clinical (MADRS, YMRS, CGI, STAI, SDS, WHOQOL-BREF) and tolerability (TSES) outcomes will be assessed every 2 weeks after FMT for 6 months. Adverse events will be verbally screened for biweekly. Stool samples will be collected at 3 and 6 months to assess fecal microbiome composition post-FMT.

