### Data management and monitoring

#### Data monitoring and auditing

A Data Monitoring Committee will identify mechanisms to ensure the safety and efficacy of all aspects of the study. This committee will review the research protocol, informed consent documents, plans for data and safety monitoring, and steps taken to maintain patient data confidentiality. Furthermore, the committee will monitor all stages of the study, including factors that may influence study quality (data quality and timeliness, participant recruitment, accrual and retention, participant risk versus benefit); consider new scientific or therapeutic evidence with implications for the safety and ethicality of the study; and review serious adverse event documentation and safety reports. Adverse events will be assessed verbally. Additionally, patients will be provided with a symptom diary covering symptoms that may indicate an adverse event related to FMT in the 7 days following the intervention. A physician will be responsible for all trial-related medical decisions and review of adverse events and severe adverse events throughout the study. All unanticipated problems will be reported to the local and main REBs. Adverse drug reactions (adverse events related or potentially related to the study project that are both serious and unexpected) will be subject to expedited reporting to Health Canada.

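### The only time contrast named for tolerability scores is baseline against week 24, which is insensitive to short-lived effects of a single FMT; the side-effect capture schedules also conflict

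*Protocol article*

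**What the plan says.** All references are to the protocol article.

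- **Exposure.** Under Intervention: "Each participant receives one dose of either autologous or allogenic FMT product". The section Intervention visit places it at Visit 3.
- **Schedule.** Table 1 heads the post-FMT period "Follow-up (12 visits every 2 weeks"), with the TSES, YMRS and symptom diary marked in the two-weekly column. Post-intervention visits says that clinical and tolerability "outcomes will be assessed every 2 weeks after FMT for 6 months".
- **Tolerability contrast.** Under Feasibility, clinical, tolerability, and safety outcomes: "Clinical and tolerability scores at baseline (Visit 2) will be compared with those at study completion (Visit 15"). Statistical methods takes the same interval, baseline to 6 months, for change scores of continuous measures.
- **Other safety provisions.** The same outcomes section bases safety on solicited and unsolicited adverse events and adds the TSES. Post-intervention visits has adverse events screened verbally biweekly. Statistical methods tests side-effect proportions between groups, without a time window, and plans models with group, time and their interaction.
- **Frequency in the abstract.** "Depressive and manic symptoms, treatment acceptability, and gastrointestinal and other side effects are assessed at baseline (prior to randomization) and weekly".
- **Diary.** Intervention visit describes a diary given after FMT, "which they will submit at every subsequent study visit". Data monitoring and auditing describes a diary "covering symptoms that may indicate an adverse event related to FMT in the 7 days following the intervention".

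**The concern.** For a single procedural exposure, the last follow-up visit is the scheduled assessment furthest from the event whose side effects are in question. A gastrointestinal reaction or a rise in YMRS that appears in the first weeks and settles contributes no change to a baseline-to-week-24 comparison. That comparison would then lean toward a conclusion of good tolerability.

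The point reaches beyond a secondary objective. Acceptability is one of the three primary outcomes, and Statistical methods derives it from reported side effects and patient outcomes. If the window for side effects is unclear, so is part of a primary outcome that is meant to inform a larger trial.

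The conflicting capture schedules add to this. A count of diary symptoms means one thing if the diary ran for a week and another if it ran for 24 weeks.

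**Working it through.** **1. Visit arithmetic, reproducing the article's own timing.** Inputs: FMT at Visit 3 (Intervention visit); 12 follow-up visits two weeks apart (Table 1). Visit 3 + k falls at week 2k, for k = 1 to 12.

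- Visit 4: week 2
- Visit 9: (9 − 3) × 2 = week 12
- Visit 15: (15 − 3) × 2 = week 24

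This agrees with the food-record timetable, where "the completed forms will be collected during visit 2 (baseline), 9 (12 weeks), and 15 (24 weeks").

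**2. What the stated contrast uses.** Visits 4 to 15 are 12 post-FMT assessments. Visit 15 is 1 of 12. The other 11, at weeks 2 to 22, do not enter that contrast, and they include the one nearest the procedure. If the abstract's weekly schedule were the true one, the contrast would use 1 of 24.

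**3. Illustration of the lost sensitivity.** The article gives no side-effect rates, so these are assumptions. With n = 30 per arm and two-sided α = 0.05,

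power = Σᵢ Σⱼ Bin(i; 30, p₁) · Bin(j; 30, p₂) · 1[Fisher p(i, j) ≤ 0.05].

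| Early rate, allogenic v autologous | Power, early or any-time comparison | Rejection at week 24 if both arms are then at 10% |
|---|---|---|
| 30% v 10% | 37.2% | 0.9% |
| 40% v 10% | 70.5% | 0.9% |
| 50% v 10% | 91.4% | 0.9% |

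The last column does not depend on the early rate, because nothing of the early difference remains in the data being compared. The table keeps 30 per arm at both times so that only timing differs. With the article's 15% dropout, week 24 would have about 30 × 0.85 = 25.5 per arm.

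**4. Capture schedules side by side.**

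- *Frequency.* The abstract says weekly. Table 1 and Post-intervention visits say every 2 weeks. Both cannot describe the same assessments.
- *Diary.* A diary limited to 7 days is finished before the week-2 visit (day 14), so there would be nothing new to hand in at the other 11 visits. Yet Intervention visit and Table 1 have it at every follow-up visit. On the 7-day reading, diary data cover 7 / 168 = 4.2% of follow-up; on the other reading they run through all 24 weeks.

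**The case against.** The quoted sentence stands among other provisions. Next to it, safety rests on solicited and unsolicited adverse events, and the TSES is added as an instrument for incidence, frequency and severity. Adverse events are screened biweekly, and a Data Monitoring Committee reviews serious events and safety reports. Statistical methods compares groups on change scores, tests side-effect proportions between groups, and plans group-by-time models that would naturally cover YMRS and TSES. Safety and tolerability are secondary objectives, and the Discussion disclaims definitive conclusions on them.

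Most of this stands, and it rules out two readings that a reader might infer:

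- *That transient effects vanish from the trial.* They do not. They would still be recorded as adverse events and in the two-weekly scores, whichever diary reading is right.
- *That the arm comparison is lost.* It is not. The Visit 2 to Visit 15 interval matches the change score that Statistical methods compares between groups.

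Nor is the absence of a mood-switch endpoint an error, since a full protocol or analysis plan may define one. The YMRS score of 12 in Eligibility criteria is a screening exclusion, not a definition of switch.

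What the objection does not remove is narrower. The side-effect proportion has no stated window, so Visit 15 remains the only time point named for tolerability scores. The longitudinal models are general, are not identified as the tolerability analysis, and, as models of mean scores, can dilute a sharp rise in a few participants. On the diary, the 7 days could be read as describing the adverse events rather than the recording period, but the article does not settle it.

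**Conclusion.** The point holds in a limited form. The named tolerability contrast draws on 1 of 12 post-FMT assessments and is insensitive to anything that resolves before week 24. The rest of the plan mitigates this but does not name a tolerability summary that is sensitive to early effects. In the illustration the difference is between 37% to 91% power for an early or any-time comparison and about 1% rejection at week 24. Those figures rest on assumed rates, full resolution by week 24 and 30 per arm; they show direction and scale and are not a forecast.

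The two contradictions, on assessment frequency and on the diary window, rest on the text alone and need no assumption. The matter should be corrected, but it does not undermine the trial's safety data collection.

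**What to change.** 1. Make the main tolerability summary a between-arm comparison, with 95% CIs, of the proportion with any new or worsened TSES item or adverse event (a) at any post-FMT visit and (b) at the first post-FMT visit, week 2.
2. State that the side-effect proportion in Statistical methods uses these windows.
3. Report the maximum post-FMT YMRS by arm, descriptively, without treating 12 as a switch threshold.
4. Keep the Visit 2 to Visit 15 comparison as one time point among the others.
5. Reconcile the assessment frequency (abstract v Table 1 and Post-intervention visits) and the diary window (Data monitoring and auditing v Intervention visit and Table 1) before diary counts are pooled.

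The cost is a few more tables and some wording; under the two-weekly schedule the data are already collected. Two cautions apply. With 32 TSES items at 12 visits there are 384 chances per participant to record a worsening, so the any-visit proportion may be high in both arms; this is why the week-2 figure should stand beside it. The intervals will also be wide: at 40% v 10% with 30 per arm, the approximate half-width is 1.96 × √(0.40 × 0.60/30 + 0.10 × 0.90/30) = 1.96 × 0.105 = 0.21, or 21 percentage points. That is acceptable in a pilot, provided it is reported as an interval.

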##### Assessment tools

The following outcome measures will be used to assess symptoms: the MADRS [19], a 10-item questionnaire which psychiatrists use to measure the severity of depressive episodes in patients with mood disorders; the YMRS [20], which is 11 items and is a clinician-administered interview scale used to assess manic symptoms; the State Trait Anxiety Index (STAI) [29], a commonly used measure of anxiety that can be used to diagnose anxiety and to distinguish it from depressive syndromes; the Clinical Global Impressions (CGI) rating scales [30], commonly used to measure symptom severity and treatment response in studies of patients with mental disorders; and the Sheehan Disability Scale (SDS) [31], a brief self-report tool developed to assess functional impairment in work/school, social life, and home life or family responsibilities domains. The World Health Organization Brief Quality of Life Scale (WHOQOL-BREF) [32], a quality of life assessment designed to be applicable cross-culturally, will also be administered.

##### Microbiome composition

Fecal microbiome profiling will be performed using Illumina sequencing. DNA extraction will be performed using a previously described protocol that enhances DNA recovery from microbial communities [33, 34], with modifications [35]. Total eubacterial load will be measured via Quantitative polymerase chain reaction (qPCR) with universal primers 8fM and Bact515R [36]. Thermal cycle reactions will run on the Bio-Rad CFX96 Real-Time System. Samples will be prepared in triplicates and quantified based on a standard curve with an efficiency of 94.9% generated by 10-fold serial dilutions of a plasmid containing a single copy of the 16S rRNA gene. The negative control includes a no template reaction to control for reagent contamination.

Bacterial community profiling of the 16S rRNA gene will be performed using paired-end reads of the V3 region using bar-coded Illumina sequencing as described previously [37] with bar codes included in the forward primer. Alternatively, amplification of the V3–V4 region will be performed using 806R primer [38]. Amplified product will be purified by separation via agarose gel electrophoresis and gel extraction. Pair-end sequencing will be performed on a MiSeq Illumina sequencer as per manufacturer’s instructions, as described previously [39].

##### Microbiome metabolomics

Fecal samples will be collected and stored at − 80°C, and fecal supernatants will be analyzed via NMR spectrometry [40].

##### Mucosal biopsy analysis

Of the two biopsies from each of the three locations, one will be stored in 10% formalin for pathological assessment and the other stored at – 80 °C for microbiome analysis. DNA will be extracted from 3 mg of tissue and purified as for the stool. Sequencing and analysis will be performed as for stool samples.

A baseline visit with the research coordinator (blind to group allocation) occurs in person, prior to the start of the active study phase, to collect baseline demographic and health service use information as well as baseline measures on mental health symptom scales. During all subsequent visits (visit 1 to visit 15), concomitant medications will be recorded. Anthropometric measurements (waist-to-hip ratio, and body mass index (BMI)) will be taken at every visit, except during the first visit for screening (visit 2—visit 15). Food intake will be recorded for 3 days (2 weekdays and 1 weekend day), and the completed forms will be collected during visit 2 (baseline), 9 (12 weeks), and 15 (24 weeks). To minimize confounding effects, participants will be asked to maintain their usual diet and exercise level. Participants will also itemize their food intake using a validated form developed by the Fred Hutchinson Cancer Research Center [41]. Food records will be readministered at 3- and 6-month time points. Dietary data will be analyzed using NUTRITIONIST PRO™ DIET ANALYSIS SOFTWARE (Axxya Systems) to assess intake of macro- and micronutrients.

##### Pre-intervention assessments

At *Visit 1*, informed written consent will be obtained, and demographic characteristics, current medical conditions and concurrent medications will be recorded. The following questionnaires will also be administered: MINI [17] for diagnosis of BD, YMRS [20] for mania, and MADRS for depression [19]. Recipients will receive instructions and two kits for collecting two stool samples at home, and a standard food record to measure dietary intake for 3 days. As diet and bowel preparation alter the microbiome, stool samples will be collected at *Visit* 2, 3 to 4 days prior to colonoscopy. A fraction of these fecal samples will be stored at – 80 °C for microbiome analysis. After randomization, 150 g of the remaining, refrigerated feces will be manufactured into FMT product. A portion of FMT fecal filtrate will be frozen at – 80 °C for future analysis, and 20mL of blood will also be collected prior to randomization for analysis if a recipient is later found to be infected with a transmissible disease. For baseline clinical scores, the following questionnaires will be given: MADRS [19], YMRS [20], CGI [30], STAI [42], SDS [31], WHOQOL-BREF [32], and the TSES [28].

##### Intervention visit

At *Visit 3*, FMT will be performed. To document side effects, patients will be provided with a symptom diary after FMT, which they will submit at every subsequent study visit.

##### Post-intervention visits

To evaluate whether FMT effects longer-term changes in depression severity and microbiome profile, patients will be followed for 6 months (24 weeks) post-FMT, during *Visits 3–15*. Clinical (MADRS, YMRS, CGI, STAI, SDS, WHOQOL-BREF) and tolerability (TSES) outcomes will be assessed every 2 weeks after FMT for 6 months. Adverse events will be verbally screened for biweekly. Stool samples will be collected at 3 and 6 months to assess fecal microbiome composition post-FMT.

### Statistical methods

We will use descriptive methods to estimate feasibility and compliance with the FMT intervention, the number of FMT and placebo treatments, the number of fecal samples provided, the duration of follow-up, recruitment rate, rates of nonparticipation, and so on. We will calculate acceptability using reported side effects and patient outcomes.

Variable distribution will be assessed using graphical methods and descriptive statistics, including means, standard deviations, medians and 1st and 3rd quartiles, frequencies and proportions, will be calculated where appropriate. Randomized groups will be compared to assess whether imbalance in covariates such as age and gender are present. For continuous measures (e.g., MADRS scores), change scores will be calculated as the difference between baseline and 6-month visit assessments. Groups will be compared using independent samples *t* test or Wilcoxon signed rank test as appropriate. For binary measures (e.g., proportion of side effects), the difference between groups will be tested using Chi-square or Fisher exact test as appropriate. Bivariate relationships between outcome measures and changes in microbiome composition (e.g., relative abundances of taxa of interest) will be explored using Spearman and Pearson correlation coefficients. For microbiome and metabolome data, multivariate dimensionality reduction approaches, such as Principal Components analysis and cluster analysis, will be employed.

Trajectory plots will be created to examine changes in outcome measures over time. Generalized linear regression models will then be used to assess differences [43] between groups at different time points, as was well as to explore the relationship between these changes and microbiome characteristics. In order to account for correlation between time points, random effects models and generalized estimating equations approach will be used. All models will include group, time, and group by time interaction terms; additionally, factors with known influence on outcome measures will be considered for inclusion as covariates, particularly if found imbalanced between the randomized groups. For patient dropout, the missingness patterns will be assessed, and appropriate methods of handling missing data will be used [44]. Goodness-of-fit will be applied for model diagnostics.

Statistical analyses will be performed using SAS 9.4, R 3.1, as well as analytic tools available in QIIME package. All tests will be two-sided with a significance level of 5%. Where necessary, *p* value adjustments for multiple testing (e.g., Bonferroni, Holm’s Bonferroni Step-down, Benjamini and Hochberg False Discovery Rate) will be employed.

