### Eligibility criteria

Eligible participants must be outpatients between 18 and 65 years of age, have a diagnosis of BD (type I or II) according to the Mini International Neuropsychiatric Interview (MINI) [17], have been on a stable first-line treatment for BD depression as defined in the Canadian Network for Mood an Anxiety Treatment (CANMAT) 2018 guidelines [18] at an adequate dose for ≥ 8 weeks prior to study entry, and currently be suffering from a depressive episode, characterized by a Montgomery–Asberg Depression Rating Scale (MADRS) [19] score at screening and baseline of ≥ 20. Patients will be excluded if they have a Young Mania Rating Scale (YMRS) [20] score of ≥ 12 at screening; meet DSM-IV criteria [21] for substance abuse within the last 6 months or lifetime dependency; have an active eating disorder; have schizophrenia or schizoaffective disorder; have chronic gastrointestinal diseases; conditions causing immunosuppression; a significant bleeding disorder; a history of incomplete colonoscopy; are pregnant or breastfeeding; have regularly used non-steroidal anti-inflammatory drugs, antibiotics, or iron supplements within 3 months prior to study entry; have used prebiotics or probiotics for medical purposes, or have taken antibiotics or any experimental drug within 3 months prior to study entry.

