### Sample size

This is a pilot feasibility trial designed to show if a larger RCT trial would be worthwhile. Therefore, no formal sample size calculation has been carried out [45]. A review by Hertzog suggests a range of 20 to 40 participants to allow for sufficient variability in acceptability assessment of an intervention [46]. Based on work from a pharmaceutical study in a similar patient population [47], the expected standard deviation of change expected in the MADRS score is approximately 12. Therefore, with 25 patients per group, we will be able to quantify the difference in change in MADRS score between groups to within 6.5 points with 95% confidence. This will allow data that can be used in the generation of a sample size for a larger trial. To account for a 15% dropout rate, we plan to recruit 60 patients; 30 will receive the active treatment (allogenic FMT), and 30 will receive the control treatment (autologous FMT).

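### MADRS is compared as an unadjusted change score, and baseline score is left to a discretionary covariate rule instead of being a fixed adjustment

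*Protocol article*

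**What the plan says.** Three statements in the protocol's Statistical methods section settle how MADRS is analysed.

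- For continuous measures, "change scores will be calculated as the difference between baseline and 6-month visit assessments". The comparison follows directly: "Groups will be compared using independent samples" t test, or a Wilcoxon test. No baseline term appears.
- For the repeated measurements, "random effects models and generalized estimating equations approach will be used", and "All models will include group, time, and group by time interaction terms". Baseline score is not among the required terms.
- Beyond those terms, "factors with known influence on outcome measures will be considered for inclusion as covariates, particularly if found imbalanced between the randomized groups". Baseline score is not named here either.

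Baseline MADRS is always available. Under Eligibility criteria, entry requires a MADRS "score at screening and baseline of" at least 20, and Table 1 schedules the scale at both visits.

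The Sample size section rests its precision statement on the raw change: "the expected standard deviation of change expected in the MADRS score is approximately 12", so that "with 25 patients per group, we will be able to quantify the difference in change in MADRS score between groups to within 6.5 points" (the half-width of a 95% interval). It adds that these data are meant to inform the sample size of a larger trial.

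**The concern.** A two-sample test on raw change fixes the slope of follow-up on baseline at 1. When the true slope differs from 1, two things follow. The comparison carries variance that a baseline covariate would remove. And, given the imbalance that randomization happened to produce, the estimate shifts by (slope − 1) × imbalance. With about 25 per arm, imbalances of a couple of MADRS points are ordinary.

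The optional covariate rule is a weak substitute. Whether baseline enters would depend partly on the observed data, so the reported difference could come from an adjusted or an unadjusted model at the analyst's choice.

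The stake is modest but concrete. The precision of this very contrast is how the protocol justifies 25 evaluable patients per arm. A larger trial that adjusts for baseline would need the residual SD or the baseline-to-follow-up correlation, and the raw change SD supplies neither.

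**Working it through.** **Inputs from the protocol.** SD of change 12; 25 evaluable per arm; two-sided 5% (Sample size; Statistical methods).

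**Assumed inputs.** The document gives no baseline SD (s0), 6-month SD (s1) or correlation (r). I take s0 from 5 to 10 and r from 0.2 to 0.5. For each pair, s1 is set so that the change SD stays at 12.

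**Step 1: the protocol's own figure.** Half-width = quantile × SD × √(2/n).
- Normal quantile: 1.96 × 12 × √(2/25) = 6.65.
- t quantile, 48 df: 2.011 × 12 × √(2/25) = 6.82.
- With 60 × 0.85 = 51 completers (25.5 per arm), normal quantile: 6.59.

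The stated 6.5 points is reproduced to within about 3%.

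**Step 2: the adjusted analysis.** Solve s1² − 2·r·s0·s1 + s0² = 144 for s1. The ANCOVA residual SD is s1·√(1 − r²), the slope is r·s1/s0, and the variance ratio is the residual variance divided by 144. Half-widths use t with 47 df (2.012), against 6.82 for the change score.

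| s0 | r | s1 | Slope | Residual SD | Variance ratio | Half-width |
|---|---|---|---|---|---|---|
| 5 | 0.2 | 11.95 | 0.48 | 11.71 | 0.95 | 6.66 |
| 5 | 0.4 | 13.09 | 1.05 | 12.00 | 1.00 | 6.83 |
| 5 | 0.5 | 13.69 | 1.37 | 11.86 | 0.98 | 6.75 |
| 6 | 0.2 | 11.66 | 0.39 | 11.43 | 0.91 | 6.50 |
| 8 | 0.3 | 11.66 | 0.44 | 11.12 | 0.86 | 6.33 |
| 10 | 0.2 | 8.93 | 0.18 | 8.75 | 0.53 | 4.98 |
| 10 | 0.3 | 10.28 | 0.31 | 9.81 | 0.67 | 5.58 |

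Over the whole grid the ratio runs from 0.53 to 1.00. With s0 of 5 or 6 the gain is 0% to 9% of variance.

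**Step 3: cost of adjusting.** Losing one degree of freedom changes the t quantile by a factor of 1.0006. Estimating the slope inflates the half-width by about √(1 + 1/46) = 1.011. The total is about 1%. In the worst cell of the table, 6.82 becomes about 6.90.

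**Step 4: conditional shift.** For a baseline difference D between arms, the change-score contrast moves by (slope − 1) × D.
- s0 = 8, r = 0.3, D = 2: (0.44 − 1) × 2 = −1.1 points. The arm with the higher baseline is credited with extra improvement.
- s0 = 5, r = 0.5, D = 2: (1.37 − 1) × 2 = +0.7 points. The direction is reversed.
- The standard error of D is s0·√(2/25): 2.26 at s0 = 8 and 1.41 at s0 = 5. An imbalance of at least 2 points in either direction then has probability about 38% and 16% respectively.

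**Step 5: do the planned longitudinal models already adjust?** The text does not say whether baseline is a response at the first time point or is left out. If it is a response with an unconstrained group-by-time term, the week-24 contrast against baseline equals the raw change difference in complete data. If it is left out and not added as a covariate, there is no baseline adjustment at all. Neither reading gives fixed adjustment.

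**The case against.** The strongest reply is that adjustment is not excluded. The covariate rule allows factors with known influence, baseline severity is an obvious candidate, and covariate lists are often left to an analysis plan, which is not shown here. That stands in part. The fair criticism is that baseline adjustment is optional and partly driven by imbalance, not that it is ruled out. It remains a criticism because the unadjusted change-score test is a stated choice, not a gap.

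Several stronger readings are tempting, and the document does not support them.

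- *The plan throws away the intermediate visits and partial follow-up.* This is true of the two-sample test only. The planned random effects models use them, and the section commits to examining missingness and handling it appropriately.
- *The change score is biased.* Over randomization it is unbiased and its interval is valid. The shift exists only conditionally on the imbalance that occurred.
- *The entry cut-off forces the slope well below 1, so the higher-baseline arm always gains.* In a linear model, selection on baseline narrows the baseline SD; it does not lower the slope. At s0 = 5 the slope passes 1 at r = 0.4, and the direction reverses.
- *Adjustment removes imprecision at no cost.* It reduces imprecision, possibly by nothing, at a cost of about 1% of the half-width.
- *Naming GEE is an error.* Its missing-data and small-sample refinements, like the choice of degrees-of-freedom method, belong in an analysis plan.

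Consequence is also limited. The listed primary outcomes are feasibility, acceptability and adherence, there is no formal sample size calculation, and the Discussion disclaims definitive conclusions on efficacy. Against that, the Background section places the examination of efficacy within the primary objective, and the precision statement concerns exactly this contrast.

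**Conclusion.** The point holds in a limited form. The protocol specifies an unadjusted change-score comparison for MADRS and leaves baseline score to a discretionary rule, although it is known for everyone randomized. Fixed adjustment is the better choice whatever the slope: asymptotically it is never less precise, and it corrects for imbalance in both directions.

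The principle is firm but the size is uncertain. The benefit ranges from almost halving the variance to none, and it rests wholly on assumed baseline SDs and correlations. A narrow baseline SD, which the entry cut-off makes plausible, puts it near the bottom of that range. The illustrative 1.1-point conditional shift is small against a half-width of 6.8. This is a worthwhile improvement to the plan, not a flaw that invalidates the trial or its primary feasibility aims.

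**What to change.** Pre-specify baseline MADRS as a covariate regardless of observed imbalance, and name one main MADRS estimate: the baseline-adjusted group difference at week 24 with its 95% confidence interval. The preferred vehicle is the random effects model already planned, fitted to post-FMT scores with group, time, group-by-time and baseline score. The minimum is an ANCOVA at 6 months. Treat the other continuous scales measured at baseline in the same way. The unadjusted change can still be reported descriptively.

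Report the residual SD and the baseline-to-week-24 correlation as well, since the larger trial's sample size will need them.

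The cost is a change of wording in Statistical methods and, for ANCOVA, about one degree of freedom, or about 1% of the half-width. No new data, visits or participants are needed.
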